**Fig. 1 Fig1:**
[figure not shown]
CONSORT for mhGAP/IPT-G Randomized Pilot Feasibility Study

**Table 1 Tab1:** Summary table the pilot feasibility trial

Objectives	Outcomes	Criterion for success	Method for analysis	Estimate of effect
Primary feasibility	Demonstrate that the method of RCT feasible in MCH clinical service context	70% of pregnant adolescent-caregiver-health care workers that are exposed to content of the intervention; 80% of data collection performed as planned;	Quantitative analysis for implementation outcomes will be based on data collected throughout the implementation period, and analyzed separately for each time point as well as jointly to create overall summary scores. Analysis for the MCH service outcomes will be based on pre-post intervention data using pair-t tests and repeated measures. Quantitative data for implementation outcomes, MCH service outcomes, and adolescent mental health effectiveness outcomes will be examined separately. Qualitative data will be transcribed and analyzed using similar techniques described in Aim 1. We will review all focus group discussion data and use grounded theory approach to search for emerging themes using open and axial coding.	Depression and family functioning will be based on multi-level modeling, adjusting for family/group nesting effects. Post-intervention effects estimated as a function of baseline levels of the corresponding outcome variables and intervention status.
Secondary outcomes	a) Identification of barriers and facilitators to mhGAP/IPT-G implementation in MCH context b) Capacity building of MCH personnel, researchers and select MOH and County health partners c) Adaptation of mhGAP/IPT-G	a. Identification of select mhGAP informed barriers to care and adaptation of mhGAP and IPT-G for this context b. Capacity building will significantly improve trainees’ (nurses and community health workers) knowledge and skills in implementation research and delivering of depression intervention. c. Adapted manual for IPT-G and algorithm for mhGAP-IG for depression for pregnant adolescents	Qualitative and ethnographic methods including mixed methods using D& I and attitudes to EBI and adolescent friendly health services Pre and post training interviews and acceptability and satisfaction the trainings Knowledge and fidelity trainings on mhGAP/IPT-G	N/A

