#### Study procedure

Figure 1 provides an overview of the pilot trial design. The two MCH clinics that we build capacity in Aim 2 will be the pilot Implementation sites. During the 1st implementation cycle (about 2–3 months), we will work with only 1 MCH clinic (Cohort 1), and then work with another MCH clinic in the 2nd implementation (Cohort 2). For each cohort, 45 pregnant adolescents with moderate to severe depression will be recruited. As the interventions will be using self-reported measures and the adolescent participants would be directly involved the intervention arms would be unmasked.

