#### Intervention implementation

Participants will be randomly assigned to IPT-G Full, IPT-G Mini, and wait-list control using computer random generator by research staff (*n* = 15 for each arm, 45 per cohort).
The IPT-G Full and Mini groups will receive the assigned interventions (8 vs. 4 sessions) developed from Aims 1 and 2 (including a perinatal depression educational material/handout). To avoid contamination, intervention for the IPT-G Full and Mini versions will be carried out by 2 separate implementation teams (2–3 facilitators in each team) follow the assigned manual/protocol. Figure 2 provides intervention contents for the Mini version, in comparison to the recommended Full version.The Control will receive standard care (with referral) and perinatal depression educational materials for safety concerns. They will receive IPT-G Mini after the post implementation assessment is completed.

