**Training of health workers and capacity building activities**	Train two-four career researchers, engage communities and build networks with Ministry of Health, mapping a referrals process for any medical or psychosocial issue arising during study	Train data collectors & RAs in two sites, train teams in psychological first aid, identify community health workers for linkages in case of any referrals for those with high depression or at risk for mental or physical	Collaborative work with the research team; three early career researchers and postgraduate students trained in mhGAP and IPT-G; technical and community advisory	Collaborative work with research team, trained researchers to train health facility workers and community health workers; capacity building of the health facility nurses in depression screening for adolescents especially peripartum	Collaborative work with the research team; trained health facility and community providers; technical and community advisory and mentors	Trained data collectors from Aim 1 would be re-engaged and additional trainings and capacity building on survey data collection will be carried out before the survey is collected. Quality assurance checks will be carried out after first 5 participant survey data per site and training repeated if there are discrepancies	Dissemination of findings to Ministry of Health and Nairobi County, Training programs for health facility workers with county and ministry of health using mhGAP
**Data collection method**	Iteratively developed mixed methods inquiry with expert consultation, community advisory support	a. FGDs, KIIs b. Short survey for conjoint experiment	a. Stakeholder engagement through advisory board meetings and group discussions, b. Expert feedback	a. ethnographic- observational study, b. training workshops with the researchers, c. training workshops in the health facilities	a. Stakeholder engagement through advisory board meetings and group discussions, b. Expert feedback	feasibility trial with individual level randomization- Intervention will be delivered in groups at the health facility and data would be collected during each session and after session	Mixed methods analysis: psychometrics/multivariate analyses/ mixed qual methods

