#### Sample size

A randomly selected sample of 90 adolescent-parent dyads will be recruited. It has been suggested that a minimum of 30 participants per group/arm is sufficient for individual IPT and IPT-G pilot studies based on similar intervention studies in LMICs [17, 18, 23].

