#### Analysis plan for the feasibility outcomes

Data collected through 2 cohorts will be analyzed. Quantitative analysis will be focused on examining the following questions:
Examine acceptability, appropriateness, usefulness, engagement, and fidelity for both full and mini versions of integrated mhGAP/IPT-G intervention implementation using task-shifting/sharing approach in MCH contexts.Examine MCH service quality change patterns before and after implementation of the mhGAP/IPT-G model will improve.Examine whether pregnant adolescents in the IPT-G will have better outcomes relative to control, but high impacts/effect size for the IPT-G Full version.

The following stop-go criteria will be used to determine whether to proceed to the main trial: the recruitment proceeds well so that the first IPT-G cohort can proceed by the end of the first month of the specified recruitment period. The IPT therapists that is the trained CHVs and nurses demonstrate adequate levels of treatment fidelity to the WHO IPT-G checklist adherence available in the manual and 70% of participants attend at least 5 of the available sessions in the course of their treatment and 80% are successfully followed up at primary endpoint.

Quantitative analysis for *implementation outcomes* will be based on data collected throughout the implementation period, and analyzed separately for each time point as well as jointly to create overall summary scores. Analysis for the *MCH service outcomes* will be based on pre-post intervention data using *paired-t tests* and repeated measures. We will examine patterns separately and jointly for two MCH clinics. Analysis for *estimating size of impact* on mental health (depression) and family functioning will be based on multi-level modeling, adjusting for family/group nesting effects. Post-intervention effects/impacts will be estimated as a function of baseline levels of the corresponding outcome variables and intervention status. Effect size (regardless the statistical testing significant level) will be computed. *Quantitative data* for implementation outcomes, MCH service outcomes, and adolescent mental health effectiveness outcomes will be examined separately.

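### The effect-size model names no clinic/cohort term, and its single family/group nesting adjustment does not fit every outcome and arm

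*Protocol article*

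**What the plan says.** The Protocol article, under Analysis plan for the feasibility outcomes, gives one sentence for both effectiveness domains: the analysis of mental health (depression) and "family functioning will be based on multi-level modeling, adjusting for family/group nesting effects". Post-intervention effects "will be estimated as a function of baseline levels of the corresponding outcome variables and intervention status". Table 1 repeats the nesting wording: "Depression and family functioning will be based on multi-level modeling, adjusting for family/group nesting effects". No other predictor is named.

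The design is set out elsewhere in the article:

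- **Clinic and cohort.** Study procedure: "we will work with only 1 MCH clinic (Cohort 1), and then work with another MCH clinic in the 2nd implementation (Cohort 2"). Clinic and calendar period are therefore one factor with two levels.
- **Allocation.** Intervention implementation: "15 for each arm, 45 per cohort".
- **Delivery.** Table 4: "feasibility trial with individual level randomization- Intervention will be delivered in groups at the health facility". Under Intervention implementation, controls have standard care and printed material, and are offered IPT-G Mini only after the post-intervention assessment.
- **Informants.** Table 2 assigns mental health measures to the adolescent alone, and family functioning to adolescent and caregiver.
- **Size.** Sample size: "A randomly selected sample of 90 adolescent-parent dyads will be recruited".

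The analysis section also says that patterns will be looked at by clinic and for both clinics together. That sentence comes straight after the one on MCH service outcomes and before the one on effect sizes.

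**The concern.** The stated model and the stated design do not line up in two places.

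1. Arm sizes are fixed within each single-clinic cohort, yet the model names no clinic/cohort term. Any outcome difference between the clinics must then go into the residual or, if a group random effect is fitted, into the group variance. Every therapy group lies wholly inside one clinic, so the model cannot distinguish a clinic gap from variation between groups.
2. One family/group adjustment is stated for outcomes and arms with different structures. Depression has one informant per family and one post-intervention value. Therapy groups exist in two of the three arms.

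At stake is the stated uncertainty of the effect sizes. The abstract asks whether the compressed version has an effect of similar size to the full one. With 30 per arm, that comparison is imprecise even when modelled well.

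**Working it through.** **Inputs from the article:** 2 cohorts (one clinic each), 3 arms, 15 per arm per cohort.

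**Assumed, because the article does not give them:** number of therapy groups per arm per clinic (one of 15, or two of 7 to 8), group ICC (0.05 unless stated), and clinic gap D in SD units (0.5 unless stated). The plan adjusts for baseline and these calculations do not, so D is best read as the gap left after that adjustment.

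**1. The plan's count.** 2 × 3 × 15 = 90, and 2 × 15 = 30 per arm. Reproduced.

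**2. Independent observations.** SE = √(1/30 + 1/30) = 0.258. 95% half-width = 1.96 × 0.258 = 0.51 SD.

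**3. Grouping in the IPT-G arms only.** The design effect for an IPT-G arm is 1 + (m − 1) × ICC. For m = 15 it is 1 + 14 × 0.05 = 1.70.
- Full versus control: √(1.70/30 + 1/30) = 0.300, half-width 0.59 SD.
- Full versus Mini: √(1.70/30 + 1.70/30) = 0.337, half-width 0.66 SD.
- For m = 7.5 the design effect is 1.325, giving half-widths of 0.55 and 0.58 SD.

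If the group effect drops out, the model reports about 0.51 in each case.

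**4. Clinic omitted, no group effect.** With balanced arms the SE is inflated by √(1 + D²/4): 1.005 at D = 0.2, 1.03 at D = 0.5 and 1.12 at D = 1.0. This is conservative and mild.

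**5. Clinic omitted, group effect fitted.** With one group per arm per clinic, each IPT-G arm has two group means. The expected variance between them is ICC + (1 − ICC)/15 + D²/2 = 0.050 + 0.063 + 0.125 = 0.238. The clinic term (0.125) is 2.5 times the true group variance (0.050).
- Group effect in Full and Mini only: SE for Full versus control ≈ √(0.238/2 + 1/30) = 0.39.
- Random intercept for every arm-by-clinic cell, controls included: the control cell variance is 1/15 + 0.125 = 0.192. The pooled value is (2 × 0.238 + 0.192)/3 = 0.223, so SE ≈ √0.223 = 0.47.
- Clinic in the model: √(0.113/2 + 1/30) = 0.30.

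A simulation (2,000 trials per setting, REML fits, no baseline covariate) agrees closely. Mean model SE for Full versus control at D = 0.5 and ICC 0.05:

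| Model | One group per arm per clinic | Two groups |
|---|---|---|
| True SE | 0.30 | 0.27 |
| Group effect in Full and Mini only, clinic in | 0.31 | 0.28 |
| Group effect in Full and Mini only, clinic out | 0.38 | 0.31 |
| Group effect in all arms, clinic out | 0.45 | 0.35 |
| No group effect, clinic out | 0.26 | 0.27 |

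With clinic out and a group effect in, coverage of nominal 95% intervals was 96 to 98%: too wide. At D = 0 the omission did no harm.

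**6. Family level.** With one adolescent report per family, the outcome variance is family variance plus residual variance, and only the sum can be estimated. With two informants, treating the reports as independent understates the SE by a factor of √(1 + r). For an assumed within-dyad correlation r of 0.2 to 0.5 that factor is 1.10 to 1.22, so the family level is needed there.

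**7. Few groups.** With one group per arm per clinic and clinic in the model, about one degree of freedom is left for the group variance. Treating the within-group variance as known, the chance that its ANOVA estimate is zero or lower is P(χ²₁ < 0.95/1.70) ≈ 54%. With two groups per arm per clinic there are 8 − 2 − 1 = 5 degrees of freedom, and the chance is P(χ²₅ < 5 × 0.95/1.325) ≈ 39%.

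**The case against.** The strongest reply is that this is a condensed article and the coding of random effects belongs in an analysis plan that is not shown. The words family/group can be read as each level where it applies, and a partially nested model is compatible with them. Effect estimation is called secondary in the methodology for the pilot trial (although the note to Table 2 calls effectiveness outcomes primary). Effect sizes are to be computed whatever their significance, no interval is promised, and the stop-go criteria do not use them. Much of this stands: degrees-of-freedom methods and ICC sensitivity runs are not findings here. What remains is that the article does name its predictors and leaves out the one factor within which its arm sizes are fixed. The sentence on patterns by clinic does not clearly reach this model.

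A reader might infer more than the documents support:

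- **That the data lack family and group nesting.** They do not. Dyads report family functioning, two arms are treated in groups, and adjusting for both is right in principle.
- **That false-positive rates are inflated.** Rates of 10% (Full-control) and 14% (Full-Mini) do arise at ICC 0.05 with one group of 15 per arm per clinic. They come from an ordinary least-squares test with no group effect, which is not the model stated.
- **That the model will fail to converge.** This has not been shown. A family level that cannot be estimated for depression would simply be dropped, and doing so does not set the group variance to zero.
- **That leaving out clinic makes intervals too narrow or biases the contrast.** It makes them too wide, and balanced allocation protects the contrast.
- **That randomisation was formally stratified.** This is only an inference from 15 per arm per cohort. The article mentions a computer random generator and no stratified procedure.

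**Conclusion.** The point holds in a limited form. Clinic/cohort is a design factor missing from the named predictors, and the nesting adjustment is stated once for outcomes and arms that need different terms.

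The two consequences run in opposite directions. With a group effect fitted and clinic left out, the mean SE for Full versus control is 0.38 to 0.45 against 0.30 (one group per arm per clinic), or 0.31 to 0.35 against 0.27 (two groups), at an assumed ICC of 0.05 and a 0.5 SD clinic gap. With no clinic gap there is no loss. If instead the group effect were dropped, the half-width of 0.51 SD would understate 0.59 (Full-control) and 0.66 (Full-Mini) at ICC 0.05 and groups of 15.

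It cannot be said that the intervals will be wrong. That depends on the number of groups, the ICC and the clinic gap, none of which the article gives. The absence of bias also assumes that balance is roughly kept among those followed up.

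**What to change.** In the effect-size paragraph and in Table 1:

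- Add a fixed effect for clinic/cohort.
- Fit the group random effect in the Full and Mini arms only, with each control as a singleton.
- Use the family level only for measures reported by both adolescent and caregiver, and not for depression or other adolescent-only outcomes.
- Record each participant's IPT-G group ID during delivery, and state the planned number of groups per arm per clinic.

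The cost is a few sentences, slightly more analysis work and one data field. The fix has a limit: with few groups the group variance is poorly estimated. In the simulation with one group per arm per clinic and ICC 0.05, even the partially nested model with clinic covered only about 91 to 93%. The effect-size intervals should be reported with that caution.

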**Fig. 3 Fig3:**
[figure not shown]
Group Interpersonal Psychotherapy full versus mini (or brief) versions

#### Data collection focus and procedures

We will conduct eight focus groups (*n* = 40) with representative diverse stakeholders (i.e., including two groups for pregnant adolescents and new adolescent mothers, two groups for adolescent caregivers and partners, two groups for MCH staff, 1 group for community advocates and policy leaders, and 1 group for child and adolescent mental health professionals). Each focus group discussion (FGD) will have about 5 participants. Each group will participate in three FGD meetings. One meeting will focus on barriers/strategies related to mhGAP-IG, and the other meeting will focus on barriers/strategies related to IPT-G. The third FGD would be focusing on mental health treatment preferences of pregnant adolescents. Each focus group will last 1½ to 2 h. Participants will participate in an FGD and complete a survey, and these will be carried out in English or Kiswahili (as English is the official language in Kenya). Focus group guides/questions and quantitative survey will be adapted from existing D&I studies [48], or existing D&I measures (see measures under sub-study 1). Stakeholders’ views on barriers and strategies in five CFIR domains will be discussed separately for mhGAP and IPT-G. Informed by our previous needs’ assessment work, strategies related to livelihood problem, partner/family engagement, knowledge gap, and stigma reduction will also be explored. Key information that we will gather from different groups of stakeholders is summarized below.
*For FGDs with adolescents and families/partners* (*n* = 20, recruited through two MCH clinics that we have partnership with from previous MCH epidemiological studies), discussion will focus on CFIR individual, intervention, and inner setting domains, and examine their knowledge related to perinatal depression, and views (including barriers and potential strategies) related to adolescent pregnancy, mhGAP/IPT-G (fit, usefulness, perceived feasibility and usefulness of IPT-G Full and Mini versions), family member/partner engagement, support, and empowerment strategies, and preference for integrated mental health-MCH services. *Eligibility criteria for adolescent participants* would be: participants of ages 13–18 years, willingness to sign consent form, being pregnant or a new mother for female participants, willing to fill the questionnaires and participate in the interviews, consent to publish the findings. For other stakeholders including health facility providers, adult caregivers, community health workers eligibility includes: above 18 years of age, willingness to sign informed consent to participate in the study and for the deliberations to be recorded, willing to engage with the issues around mental health and adolescent pregnancy conducted through survey or interviews, and consent to publish the findings.*For FGDs with MCH providers/staff and mental health professionals* (*n* = 15, recruited through the two MCH clinics [same as the sites for family recruitment] and mental health professional networks), discussion will focus on the CFIR inner setting, individual/staff, intervention, and process domains. We will examine fit, barriers, and implementation strategies for mhGAP and IPT-G implementation in MCH settings (e.g., collaborators’ roles, task-shifting/sharing strategies, workflow logistic/coordination strategies), staff attitude/belief toward EBI practices, perceived effectiveness, and MCH implementation climate.*For FGDs with the community advocates and policy stakeholders* (*n* = 5, recruited through Ministry of Health and NGO networks), discussion will focus on the CFIR intervention, process and outer setting domains, and examine barriers and strategies related to mhGAP and IPT-G. In addition, community awareness/public educational and stigma reduction strategies (outer setting strategies) will be explored to facilitate community support to address adolescent pregnancy and maternal mental health needs, which also has implications for public health impact promotion [49, 50].

Results from this study will be used to inform the adaptation of mhGAP and IPT-G contents, adolescents/ family members’ engagement activities, implementation process, and training of the implementation team. An adapted manual for mhGAP-IG and IPT-G (Full and Mini versions) will be developed.

### Methodology for sub-study 2

To better identify mhGAP/IPT-G workflow barriers and strategies in MCH contexts, MCH site visits and workflow observation will be arranged for the Community and Technical Advisory Board members (*n* = 22) (see Table 3). The observation will focus on MCH structure and perinatal service workflow. For the four adolescent representatives, we will seek two pregnant adolescents and two new adolescent mothers. The eligibility criterion would be as follows: willing to consent to participate, one pregnant adolescent and one new mother between ages 13–16, another pregnant adolescent, and new mother between ages 16–18 willing to join the meetings held at the community center or at the health facility. For all other stakeholders of the community advisory, the eligibility would be as follows: to sign informed consent to participate in the study and for the deliberations to be recorded, willing to engage with the issues around mental health and adolescent pregnancy, and willing to commute to the health facility or community center for meetings three times a year. Additionally, there would be a technical advisory board. The technical advisory board comprises of members whose organizations provided support letters during the grant and formally committed to providing technical guidance. Their eligibility includes the following: adults above 18 of years and technical persons representing mental health and health policy implementing partners in Kenya, willing to sign consent form for participation in the study, and willingness for discussion to be recorded. This will allow the Board and research members to gain better understanding about the clinical set up, implementation barriers and strategies, which will facilitate better and more sustainable workflow plan/strategy development to support mhGAP/IPT-G implementation. To ensure confidentiality, informed consent for all participants will be obtained prior to the data collection. Participating provider personnel and family members will be compensated for their time. Participating mental health professionals and officers of NGO/ Ministry of Education/ Ministry of Health will also be compensated.

Results from sub-studies 1 and 2 will be used to inform the adaptation of mhGAP/IPT-G implementation protocol in MCH context and training manual development for mhGAP/IPT-G implementation. Additional feedback will be sought from Advisory Board before using these.

